## Abstract

**Background:**

Joint replacement provides significant improvements in pain, physical function, and quality of life in patients with osteoarthritis. With a growing body of evidence indicating that frailty can be treated, it is important to determine whether targeting frailty reduction in hip and knee replacement patients improves post-operative outcomes.

**Objectives:**

The primary objective is to examine the feasibility of a parallel group RCT comparing a preoperative multi-modal frailty intervention to usual care in pre-frail/frail older adults undergoing elective unilateral hip or knee replacements. The secondary objectives areTo explore potential efficacy of the multi-modal frailty intervention in improving frailty and mobility between baseline and 6 weeks post-surgery using Fried frailty phenotype and short performance physical battery (SPPB) respectively.To explore potential efficacy of the multi-modal frailty intervention on post-operative healthcare services use.

**Methods/Design:**

In a parallel group pilot RCT, participants will be recruited from the Regional Joint Assessment Program in Hamilton, Canada. Participants who are (1) ≥ 60 years old; (2) pre-frail (score of 1 or 2) or frail (score of 3–5; Fried frailty phenotype); (3) having elective unilateral hip or knee replacement; and (4) having surgery wait times between 3 and 10 months will be recruited and randomized to either the intervention or usual care group. The multi-modal frailty intervention components will include (1) tailored exercise program (center-based and/or home-based) with education and cognitive behavioral change strategies; (2) protein supplementation; (3) vitamin D supplementation; and (4) medication review. The main comparative analysis will take place at 6 weeks post-operative. The outcome assessors, data entry personnel, and data analysts are blinded to treatment allocation. Assessments: feasibility will be assessed by recruitment rate, retention rate, and data collection completion. Frailty and healthcare use and other clinical outcomes will be assessed. The study outcomes will be collected at the baseline, 1 week pre-operative, and 6 weeks and 6 months post-operative.

**Discussion:**

This is the first study to examine the feasibility of multi-modal frailty intervention in pre-frail/frail older adults undergoing hip or knee replacement. This study will inform the planning and designing of multi-modal frailty interventional studies in hip and knee replacement patients.

**Trial registration:**

ClinicalTrials.gov
NCT02885337

**Electronic supplementary material:**

The online version of this article (10.1186/s40814-018-0316-2) contains supplementary material, which is available to authorized users.

## Background

Osteoarthritis (OA) is one of the most common chronic conditions worldwide and a major cause of morbidity, physical limitation, disability, and health care utilization [1, 2]. In 2010, the aggregate cost of managing OA in Canada was $10.2 billion [3]. It has been demonstrated that joint replacement provides significant improvements in pain, physical function, and quality of life in patients with OA [4, 5]. In Canada, during 2015–16, there were approximately 53,000 hip replacements and 64,000 knee replacements representing a 5-year increase of 18.1 and 15.7 5%, respectively [6]. It is expected that the number of older adults seeking total joint replacement will continue to rise [7].

Frailty is common in patients undergoing joint replacement [8] and refers to a medical syndrome characterized by “diminished strength, endurance, and reduced physiologic function” and with multiple causes and contributors [9]. Pre-frailty is an intermediate stage between non-frail and frail. Adverse outcomes associated with frailty include increased risk for functional disability, hospitalization, fractures [10], admission to long-term care, and increased mortality [11–14]. Frail older adults undergoing surgery are also more vulnerable to peri-operative stressors and are at increased risk of post-operative complications, increased length of stay, and discharge to assisted living [15, 16]. Recently, the Society for Perioperative Assessment and Quality Improvement recommended preoperative frailty screening evaluation and management [17]. With a growing body of evidence indicating that frailty can be treated [9] and improved [18], there is a need to examine whether targeting frailty reduction can improve the outcomes of pre-frail or frail adults who are undergoing joint replacement surgery.

Preparing patients for hip or knee replacement surgery through a prehabilitation model should be an integral part of the surgical care [19]. A recent systematic review and meta-analysis [20] examined the impact of preoperative physiotherapy on recovery after hip or knee joint replacement. Wang et al. pooled data from 22 RCTs (*N* = 1492 patients, mean age ranged from 51 to 76 years) and found that exercise/education slightly reduced pain scores within 4 weeks postoperatively and improved scores on the Western Ontario and McMaster Universities Arthritis Index at 6–8 and 12 weeks. There was no difference in SF-36 scores, length of stay, and total cost [20]. Another systematic review and meta-analysis [21] aimed to determine the effect of pre-operative interventions (exercise with or without education program) in patient waiting for hip and knee replacement. Wallis et al. included 23 RCTs (*N* = 1461 patients, mean age is 67.2 years) and concluded that exercise reduced pain for patients waiting for hip or knee replacement, and exercise with education programs improved activity after hip replacement [16].

Potential limitations of all the previous RCTs that examined pre-hip or knee replacement interventions include (1) none of these studies identified prefrail or frail population, (2) none used multi-modal interventions, (3) the duration of the interventions ranged between 2 and 8 weeks in length (a longer intervention period may improve post-operative and long-term outcomes), (4) most participants were waiting for only knee (not hip) replacement, (5) most studies were at high risk of bias. For example Wang et al. included 18 out of 22 studies with high risk of bias [20], thus, high quality RCTs are needed, and (6) most of the studies did not report critical outcomes such as frailty and treatment adherence [20].

Since, frail individuals are at greater risk of post-operative complications [15, 16], it is important to implement strategies to improve the “fitness” of frail patients pre-operatively. While previous studies with single interventions have demonstrated some effectiveness [15], multi-modal approaches have not been examined in individuals undergoing joint replacement surgery. International consensus guidelines [9] recommended an evidence-based multi-modal approach (including exercise, protein-calorie supplementation, vitamin D, and reduction of poly-pharmacy) to target frailty pre-operatively. The proposed study is a pilot RCT comparing a pre-operative multi-modal frailty intervention to usual care among pre-frail/frail patients undergoing unilateral elective total hip or knee replacement surgery. The current report outlines the research design and protocol for evaluating this pilot RCT.

### Theory and development framework

The cycle of frailty model proposed by Fried et al. 2001 (Fig. 1), identified key elements of frailty [11]. The core elements of the Fried frailty cycle incorporated the main frailty markers, including age-associated declines in lean body mass, strength, endurance, balance, walking performance, and low activity. The proposed intervention components aim to improve all the frailty markers of the Fried frailty cycle [11]. As this is the first study to implement preoperative multi-modal intervention, a pilot study is required to assess the fidelity of intervention delivery and the feasibility of (1) study process (recruitment and retention rate), (2) study resources (required time and budget), (3) management (study personal and data management), and (4) scientific (treatment safety, and estimation of potential treatment effect and its variance) [22].

**Fig. 1 Fig1:**
[figure not shown]
Cycle of frailty

### Objectives

The primary objective is to examine the feasibility of a parallel group RCT comparing a preoperative multi-modal frailty intervention to usual care in pre-frail/frail older adults undergoing elective unilateral hip or knee replacement. The secondary objectives areTo explore potential efficacy of the multi-modal frailty intervention in improving frailty and mobility between baseline and 6 weeks post-surgery using Fried frailty phenotype and short performance physical battery (SPPB), respectively.To explore potential efficacy of the multi-modal frailty intervention on post-operative healthcare services use including hospital length of stay, rate of complication after hip or knee replacement, readmission to the hospital, and number of emergency room (ER) visits.

## Methods/Design

### Study design

Fit Joints study is a pilot parallel group RCT comparing a 3–10 months, pre-operative multi-modal frailty intervention, and usual care among pre-frail/frail patients undergoing total hip or knee replacement surgery.

The main group comparisons will occur at 6 weeks post-operative. Both groups will also be assessed at 6 months post-operative. The trial has been registered with Clinical

Trials.gov NCT02885337. We used the Standard Protocol Items: Recommendations for Interventional Trials (SPIRIT) guidelines to guide the reporting of our trial protocol [23]. A SPIRIT Checklist is provided as Additional file 1, and a flow diagram is included as Fig. 2.

**Fig. 2 Fig2:**
[figure not shown]
Standard Protocol Items Recommendations for Interventional Trials (SPIRIT) Schedule of enrolment, interventions, and assessments

### Study setting

We are recruiting participants from the Regional Joint Assessment Program [24] (RJAP) at a tertiary care academic hospital (Juravinski Hospital) of Hamilton Health Science—Hamilton, Ontario, Canada. RJAP program serves patients with arthritis referred from primary care physicians to be assessed for hip or knee joint replacement by advanced practice physiotherapists (APPs) (physiotherapist with a special orthopedic training) and orthopedic surgeons [24]. After recruitment, the intervention will take place in a community setting, including the participant’s home and community centers.

### Eligibility criteria

Participants will be included if they are (1) ≥ 60 years old; (2) pre-frail (score of 1 or 2) or frail (score of 3–5; Fried frailty phenotype [11]); (3) receiving elective unilateral hip or knee replacement; and (4) waiting time to surgery is estimated to be between 3 and 10 months. Participants will be excluded if reported as having (1) renal insufficiency (due to potential contraindication of additional protein); (2) neuromuscular disorder; (3) active cancer; or (4) any inflammatory arthritis.

### Recruitment strategy

After the APPs and orthopedic surgeons assess patients referred for hip or knee problems, APPs will explain the study, invite potential participants, and screen them for eligibility. A research assistant will help the APPs in administering the Fried frailty phenotype. If eligible participants are considering the study and need time to decide, they receive the study information sheet and will be contacted by a research assistant to confirm their participation. The clinic administrations (who are blinded to the patient participation in the study) place the patients in the surgery wait list and assign them a surgery date later.

### Randomization and consent

Once the study research assistant confirms the patient’s eligibility, and obtains informed written consent, the research assistant will submit the eligibility form, consent form, and participant contact form to a team member (who is not part of the study) who will randomize the participant to the intervention or usual care group based on stratified block randomization list. To ensure an equal number of participants in the study groups, the allocation ratio will be 1:1. Participants will be stratified based on their age (≥ 80 or ≤ 79 years) and approximate waiting time (≥ 6 or < 6 months). The allocation sequence will be computer generated using SAS 9.3 software [25]. To conceal the sequence, only a researcher who is not involved in the study will have the computer-generated allocation list.

After randomization, a blinded outcome assessor will contact the participants to set up an appointment for the baseline assessment. After the baseline assessment, the study research coordinator will inform the participants of their study group. The intervention group participants will be contacted by the study intervention kinesiologist to arrange the first intervention visit.

Those blinded to the intervention will include the outcome assessors who conduct assessments at the RJAP and in participant homes, the clinic administration, data entry personnel, data analysts who performs the final data analysis, the investigative team, and members of the steering committee. The patient will also be blinded at the baseline assessment. The study coordinator, study intervention kinesiologist, and participants will not be blinded.

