**Fig. 3 Fig3:**
[figure not shown]
Study intervention and outcome assessments. The square means a visit and the circle means a phone call

Participants in the intervention group will receive, for up to 10 months, a multimodal program intended to target frailty reduction (as described in Table 1) between randomization and their surgery. The study intervention kinesiologist will manage the coordination of the exercise components of the intervention, and deliver vitamin D and protein supplementation. The study geriatrician will provide the medication review component, and 2 of the study investigators who are expert in nutrition will review the vitamin D and protein supplementation.

**Table 1 Tab1:** Components of the multimodal intervention

Component	Dose/material provided	Description
Exercise and coaching	Based on Canada’s Physical Activity Guidelines^1^ Minimum: 3× week for 45–60 min at home and/or YMCA [28, 44]	• Kinesiologist assessment: goal setting, cognitive behavior change strategies^2^ • HOME: tailored exercise program based on individual ability and exercise preference (i.e., chair versus standing exercises). Functional movements to mimic ADL’s (i.e., getting up from a chair). Exercise bands will be provided. • All participants will progress based on their current physical activity levels while focusing on personal fitness and health goals set at the beginning of the program. • YMCA: InMotion program • GOAL: endurance, resistance, and balance training 3× week for 45–60 min at home and/or YMCA • Monthly kinesiologist visit/bi-weekly phone calls [28]. • Participants will track their exercise in a study-tracking logbook.
Protein	1–2 Ensure Enlive™ protein daily	• Each serving (vanilla or chocolate flavor) contains 350 kcal, 20 g protein, 1.5 g β-Hydroxy β-Methylbutyrate (HMB) • Advised to take the protein supplement with a meal or within 3 h of exercise on activity days [32, 33]. • Pre-albumin serum level tested at the screening and 6-week postoperative visits (carried out by the clinic nurse during these visits).
Vitamin D	1 × 1000 IU/day, unless prescribed otherwise by family physician.	• Vitamin D3 (1000 IU tablets) • Serum 25 (OH). Vitamin D serum level tested at the screening and 6-week postoperative visits.

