Medication review		• A pharmacist trained geriatrician ([name]) will review the medications of participants in the intervention arm using subsets of Beers [45] and STOPP/START criteria [46] to check for any inappropriate medications. • Any recommendations will be mailed/faxed to the participants’ family physicians for their consideration by the central site coordinator.

^1^Based on Canadian Physical Activity Guidelines for those aged 65 years or older which recommend cardiorespiratory, strength, balance, and flexibility exercise components [25]

^2^Topics to support patients in achieving their health goals could include (1) goal setting, (2) self-monitoring, (3) time management, (4) overcoming barriers, (5) environmental scan, (6) social support, and (7) stimulus control

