### Study outcomes

#### Primary outcome: feasibility

Feasibility will be assessed by (1) recruitment rate, (2) retention rate, and (3) data collection completion [22]. Figure 2 summaries the primary and secondary outcomes and measurement time. The Fit Joints intervention fidelity (the degree to which the Fit Joints intervention is delivered) will be assessed by measuring the length of the intervention and number of intervention components delivered by the study kinesiologist. We will measure participants’ adherence to each component of the intervention (center-based or home exercise, protein and vitamin D supplement, and medication review). Adherence will be measured by a monthly self-reported form developed specifically for the Fit Joints trial.

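### The investigative team is declared blinded although the medication review requires knowing the arm, and analyst blinding cannot last through the adherence and exercise-setting analyses

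*Protocol article*

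**What the plan says.** The protocol article states blinding in two main places.

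- Under Randomization and consent, the blinded group includes the "data analysts who performs the final data analysis, the investigative team, and members of the steering committee". Data entry staff, outcome assessors and clinic administration are also on that list. The complement follows: "The study coordinator, study intervention kinesiologist, and participants will not be blinded".
- The abstract is shorter and omits investigators: "The outcome assessors, data entry personnel, and data analysts are blinded to treatment allocation".

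The section on the intervention components gives roles to people other than the coordinator and kinesiologist. On medications it says: "The study geriatrician will provide the medication review component". On supplements, the same paragraph assigns a task to members of the team: "2 of the study investigators who are expert in nutrition will review the vitamin D and protein supplementation". Table 1 says of the geriatrician that he or she "will review the medications of participants in the intervention arm using subsets of Beers" and other criteria, with recommendations passed to the participants' family physicians.

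Under the primary outcome, adherence is measured for each intervention component: "Adherence will be measured by a monthly self-reported form developed specifically for the Fit Joints trial". The Data analysis section uses adherence to define a per-protocol set (70% of exercise sessions and of each supplement, plus a completed medication review). It also plans a subgroup analysis by exercise setting, home or center.

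**The concern.** The blinding statement makes no exception for any investigator, and its list of unblinded people reads as complete. The intervention section describes work that at least one further person cannot do while blinded. The planned analyses also need variables that mark the intervention arm, while the analysts are described as blinded without limit.

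Two things are at stake. The trial could be reported as investigator- and analyst-blinded beyond what its own procedures allow. And decisions that involve judgement (classifying complications, forming analysis sets, choosing models, handling missing data) could be made by someone who knows the arm. With several exploratory clinical outcomes, two subgroup analyses and a per-protocol analysis in a small sample, such decisions can move results that are meant to inform a multi-center trial.

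**Working it through.** No formula decides this point; it rests on comparing sections. The one design figure is used only for size.

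**Size of the arm.** The Sample size section gives 62 for a 95% interval of ±10% around 80%. Check: n = z²p(1−p)/w² = 1.96² × 0.80 × 0.20 / 0.10² = 61.46, rounded up to 62, which agrees with the plan. With 1:1 allocation, 62 / 2 = 31 per arm.

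**Step 1: the geriatrician.** The review covers intervention-arm participants, and advice goes to their own physicians. The reviewer handles named participants who are known to be in that arm, so allocation is known. If the geriatrician belongs to the investigative team, the statement that the team is blinded is wrong. If not, an unblinded person is missing from the list. The text needs correcting on either reading.

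**Step 2: the two nutrition investigators.** The article calls them study investigators, so they fall within the team declared blinded. What they review is less clear.
- Participant-level review: they know allocation. The context favors this reading. The sentence stands beside the individual medication review, and Table 1 lets the number of protein servings vary and allows vitamin D to differ where a family physician prescribes otherwise.
- Review of the products or regimen only: they need not know allocation.

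The restriction to the intervention arm in Table 1 is written for the medication review, not for this one.

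**Step 3: count.** Certain: 1 person (the geriatrician). If the supplement review is individual: 1 + 2 = 3. Each could know allocation for about 31 of 62 participants.

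**Step 4: the analysts.** The table shows what each planned analysis needs.

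| Analysis | Intervention-specific data needed | Can coded arms stay masked? |
|---|---|---|
| Intention-to-treat comparison | None from the adherence form | Yes, if those data are withheld |
| Per-protocol set | Supplement and exercise adherence, medication review done | No: medication review is an intervention-arm activity |
| Home versus center exercise | Setting chosen with the kinesiologist at the first intervention visit | No |

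Analyst blinding is therefore possible for the main comparison and impossible for the other two.

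**Step 5: data entry staff.** The article does not say who enters the adherence forms. The unblinded coordinator could do so. No contradiction can be shown here.

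**The case against.** The strongest case on the other side has four parts.

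- **Much of the blinding is untouched.** This stands. A reader might infer from the conflict that the stated blinding does not exist at all. The article does not support that: nothing set out above contradicts the blinding of outcome assessors, clinic administration or the steering committee, and assessor blinding matters most for grip strength, gait speed and SPPB.
- **The nutrition investigators may see no individual data.** This stands as a limit. A reader might also infer that three investigators certainly know the arms. Only the geriatrician's knowledge is certain, and the article does not say that the geriatrician is an investigator.
- **Form entry, database access and order of analysis belong in a fuller protocol or analysis plan.** This stands for data entry, and the absence of those details is not the finding. It does not rescue the analyst claim, which the article makes without limit while also planning analyses that break it.
- **The consequence is modest.** Primary outcomes are recruitment, retention and data completion, reported as percentages with intervals. Efficacy is exploratory, and no section gives these reviewers a role in classification or modeling. This lowers the stakes. But no section excludes them from such a role either, because all are assumed blinded.

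Some exercise and supplement data are not automatic arm markers, since controls may attend exercise programs and the healthcare-use form also records supplements and home exercise. The study's own adherence form and the medication-review field are different: they relate to the intervention itself.

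**Conclusion.** The point holds in a limited form. The blinding statement is wrong as written for the geriatrician, who is unblinded and unlisted. It is probably wrong for two members of the investigative team, on the assumption that they review supplementation per participant. Analyst blinding can hold for the intention-to-treat comparison if intervention-specific data are withheld until it is finished. It cannot hold through the per-protocol and exercise-setting analyses.

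The size is 1 to 3 unlisted unblinded people, each potentially knowing about 31 of 62 allocations. No amount of bias can be calculated from the document, and none is claimed. The feasibility outcomes have little evident exposure; the exploratory clinical comparisons have more. The correction should be made because it is cheap and protects those comparisons.

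**What to change.** 1. In Randomization and consent, add the study geriatrician to the unblinded list. State whether the two nutrition investigators see participant-level data; if they do, list them too. Replace the blanket claim for the investigative team with one that covers its remaining members.
2. Keep those listed out of outcome classification, decisions on analysis sets and choice of model.
3. Have the analyst complete and date the intention-to-treat analysis on coded arms before adherence, medication-review and exercise-setting data are released.
4. Describe the per-protocol and home-versus-center analyses as not blinded, and limit the analyst-blinding claim in the abstract and methods to the main comparison.

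Cost: a few sentences, a small restriction on data access (for example through REDCap permissions) and a fixed order of analysis, with no extra staff or participants. The reported blinding will look slightly less favorable.
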